#### Recruitment

Based on preliminary and exploratory studies [7, 8, 45, 53, 54], we observed high participation rates in seroprevalence surveys (93% to 100%) and the finger prick in children to collect blood samples was well accepted [45, 53–56]. During door-to-door enrolment visits the research teams will be assisted by community workers and volunteer facilitators to explain the aim and importance of the research to families. The starting point of household recruitment will be the centroid (as determined by QGIS) of each selected cluster with a radial pattern of household recruitment from the starting point, following the pattern of city blocks within the cluster.

Eligibility criteria of the household and individual will be verified. The goals of the study and all procedures will be detailed following a pre-established script, the consent forms will be explained, and we will allocate adequate time to answer any prospective participant questions. Immediately after enrolment and consent of participation, entomological data collection and/or blood collection, as well as questionnaires administration will occur.

### Assignment of interventions

#### Cluster selection

In Fortaleza, there are 3020 census tracts with approximately 230 households and 810 individuals in each census tract (Fig. 3).

**Fig. 3 Fig3:**
[figure not shown]
Map of Fortaleza

Each census tract or cluster will be enumerated and the cluster eligibility criteria will be applied. Following the identification of eligible clusters, a proportionate stratified random sample of eligible clusters will be conducted. The stratification will be based on a dengue risk index calculated from the cumulative incidence of dengue notifications from 2016 to 2018 per neighbourhood or bairro, available from the Fortaleza Municipal Health Secretariat [57]. Census tracts within each bairro will be assigned to the same risk strata. Furthermore, a 400 m buffer for each cluster will be used to reduce contamination, creating a 800 m minimum distance between clusters. Clusters within that boundary area will be replaced by the next cluster, from a ranked list based upon stratification criteria [58].

#### Allocation

After both baseline collections, the rate of IgG seroconversion of each cluster will be calculated. Based on the overall distribution of seroconversion rate, there will be five risk strata created and each cluster from the baseline assessment will then be assigned to a risk stratum. A computer generated (block) randomization of each enumerated member of the strata will be assigned to either the intervention or control arm.

#### Blinding

Study participants will be aware of their assignment given that active participation in research design and activities will be encouraged for participants in the intervention group, whereas participation of those in the control group will not be solicited. Research staff involved in data collection will be blind to intervention assignment although intervention assignment may be revealed through interaction with the participants. During the analysis, all data will be anonymized, and research staff involved will be blinded to group assignment.

#### Contamination

Despite the protective measure of excluding clusters that are within 800 m from another cluster, there will likely be contamination through people interacting between the clusters at the individual or household level and through schools [8]. In addition, mosquitos from neighbouring households may influence rates in the intervention sites and children may get bitten by infected mosquitos outside of their intervention site. Both types of contamination will reduce the measured difference between control and intervention clusters although we will document the spread of intervention beyond the intervention clusters by monitoring any changes in behaviors within households and at the cluster level. Furthermore, we will collect school data from participating children including GPS coordinates for the schools and identify if the school is in a control or treatment area. This information will be included in the final analysis to estimate the impact of potential contamination on our findings.

### Data collection methods

#### Blood samples

Dried blood spot (DBS) samples will be collected at baseline and follow-up visits by trained nurse technicians, according to aseptic measures using disposable contact activated lancet and gloves. Finger prick will be used to facilitate the sampling procedure for children. A thin layer of lidocaine gel (topic local anesthetic) will be applied to ease the sting of the prick [59]. Expressed blood drops will be placed on filter paper [60–63]. All samples will be anonymized with study ID code upon collection and will be stored and labeled using barcoded stickers. Samples will be stored individually in a resealable plastic bag in a refrigerator between 4 °C and 1 °C until processing for analyses. DBS elution will be diluted for enzyme-linked immunoabsorbent assays (ELISA) using Panbio Dengue IgG Indirect ELISA kits for the detection of IgG antibodies to dengue antigen serotypes (1, 2, 3 and 4) in serum.

#### Entomological assessments

Each participating household will be inspected by entomological workers for all indoor and outdoor containers (tires, flower vases, water storage barrels, laundry wash basins, plastic tarps, puddles, and discarded containers such as bottles, cans, drums, metal pots, and plastic containers) including natural habitats such as tree holes and leaf axils [8]. Entomological surveys will also be conducted in elementary schools, identifying high-risk areas for breeding sites within each school as well as high-risk areas within the cluster (e.g., waste collecting bins, scrap yards, vacant lots, landfills). Schools and households will also have a premise condition index, which is based upon the house or school structure conditions (e.g., well-maintained) and yard conditions, if applicable, (e.g., well-maintained), which will range from 0 to 6 [64]. All containers will be classified according to size and use (routinely used or not in use), and presence (based on visual inspection) of larvae and/or pupae, which will be used to calculate the container index (number of positive containers per household). Adult mosquito collection will be conducted for each household using Prokopact aspirators, for a collection time of 1 h for both inside and outside of the home. Captured mosquitos will be stored on wet or dry ice in an insulating container and transported to the laboratory where all adult female *Aedes aegypti* and *Aedes albopictus* will be identified and stored. This will be used to calculate the number of adult female *Aedes* mosquitos per household. Ambient temperature and relative humidity will be recorded for each household during the entomological surveys using an iButton sensor.

#### Household survey

A questionnaire will be administered to a principal adult respondent by a trained interviewer during the entomological inspections and will include questions about: sociodemographics; recent dengue episodes; KAP [49] with respect to dengue and dengue control practices; social capital; acceptability [65] and participation in research activities. The wet season baseline will be shorter in length, focusing on recent dengue episodes and KAP.

#### Community focus groups and interviews

There will also be a series of focus groups convening representatives from six intervention communities as well as individual interviews, with a subsample of people with opinions on vector control interventions (principle of purposeful sampling, criterion-i) [66]. Intervention communities will be self-identified neighbourhoods that are not confined to the intervention clusters [7] although eight intervention clusters will be randomly chosen, according to a risk index which will be created from the baseline data using principal component analysis. The eight clusters will be selected to represent the range of heterogeneity of risk amongst the intervention clusters. Clusters will be used as a starting point in identifying intervention communities.

Focus groups, with at least 4 groups of 8 to 10 individuals each, will include representatives from each intervention community that will meet every 6 months. Individual interviews (25 to 30 people) will be conducted with key stakeholders from each intervention community every 6 months with data saturation taken into consideration. This information will be used for a series of analyses including process, social acceptability, fidelity, empowerment, and realist. All focus group and interviews will be carried by researchers in social sciences who will record, transcribe and analyse the data according to the framework analysis and realistic evaluation process [65, 67].

#### Document analysis

For the fidelity analysis [46, 68], a process documentation system will be created. Implementation communities will be identified post-allocation and the types of actors involved in each component or intervention activity. The critical points for assessment in the implementation process will be identified and self-report forms will be created based on specific descriptors of fidelity to the intervention (i.e. details of content, processes, frequency, duration, coverage) which will be completed by facilitators in each community. A purposive heterogeneous sample of the actors involved in the implementation will be trained in completing the forms systematically while implementing the interventions. The self-report forms will be collected every 6 months, coinciding with household data collection.

#### Data quality assurance

For serological analyses, the assay will be run with controls and cut off samples (quality control procedure) included within the ELISA kit and once the assay passes the quality control measures, unique samples will be tested. For individual with samples that seroconvert during follow-up, both samples from baseline and follow-up will be tested again in the same assay plate as controls for confirmatory testing. In addition, paired samples (baseline and follow-up surveys) will be used as procedures control to validate time consistency in the laboratory analyses. A random subsample of 10% of seroconverted samples for anti-DENV IgG will undergo PRNT for confirmation of infection, verify cross reaction with other arboviruses and serotyping. For the entomology samples, a chief lab entomologist will validate counting and classification by species for 1% of all samples.

Standard Operating Procedures (SOPs) will be adapted from previous studies and implemented for all procedures included in that trial. All research members and personnel will adhere to strict data quality assurance processes. At the beginning of trial preparation, a workshop will be held in Brazil for research members to discuss and develop guidelines and SOPs for research staff and field teams. The procedures’ stringent application will be supervised by the field coordinator. A two-day training session will be held for each field team to ensure good practice during data collection. The training will include different modules according to personnel needs: recruitment and interviews techniques, blood collection, entomological data collection, electronic data collection, confidentiality, and qualitative data collection. There will be field supervisors for blood collection, household surveys, entomological surveys, and qualitative data to ensure high quality data collection. Further quality assurance steps are described in the data monitoring section.

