#### Outcomes

Primary outcomes are: rates of anti-dengue Immunoglobulin G (IgG) seroconversion (from negative to positive at follow-up) to evaluate the incidence of primary infections, and adult female *Aedes* density (number of adult female *Aedes* per household). Additional measurement of the antibodies waning rate or disappearance of detectable IgG antibodies (from positive at baseline to negative at follow-up), which may happen one to 2 years after primary dengue infections will determine the impact of the intervention on subsequent dengue secondary infections [48]. Secondary outcomes captured during household visits at baseline and follow-up are: i) anti-dengue IgG antibodies waning rates; ii) self-reported dengue during the most recent dengue season; iii) entomological indices: the container index (number of positive containers per household) and the premise condition index (how well the structure is maintain and yard), and, iv) knowledge, attitudes, and practices (KAP) for dengue control that will combined to create an index [49]. Secondary outcomes captured from the household survey, community focus groups, and in-depth individual interviews include: i) social acceptability of activities; ii) implementation fidelity and adaptability processes; iii) potential for sustainability, and iv) empowerment of individual and communities.

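### Same-plate confirmation is specified only for negative-to-positive IgG changes, so the waning outcome is more exposed to single-test error than seroconversion

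*Protocol article*

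**What the plan says.** The Outcomes section of the protocol article uses IgG changes in both directions.

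- The primary serological outcome is "rates of anti-dengue Immunoglobulin G (IgG) seroconversion (from negative to positive at follow-up".
- The reverse change is described as "disappearance of detectable IgG antibodies (from positive at baseline to negative at follow-up), which may happen one to 2 years after primary dengue infections". It is the first listed secondary outcome, "i) anti-dengue IgG antibodies waning rates", and the article says that measuring it "will determine the impact of the intervention on subsequent dengue secondary infections".

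The Data quality assurance section describes four laboratory controls.

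- Every assay carries the kit's own controls and cut-off samples and must pass before study samples are read.
- Apparent seroconverters are rerun: "For individual with samples that seroconvert during follow-up, both samples from baseline and follow-up will be tested again in the same assay plate".
- A general check across surveys is planned: "paired samples (baseline and follow-up surveys) will be used as procedures control to validate time consistency in the laboratory analyses".
- Neutralisation testing is limited to one in ten of the seroconverted samples, drawn at random.

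The second and fourth controls are limited to seroconverters. The first and third are not, but neither is said to confirm or change an individual child's result.

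**The concern.** A change between two visits is wrong if either reading is wrong. The plan recognises this for seroconversion and removes the plate-to-plate component by rerunning both samples together. The same reasoning applies to a change from positive to negative: a falsely positive baseline, a falsely negative follow-up or a value close to the cut-off is counted as waning.

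The two first readings very probably come from different runs. The serological surveys are yearly (Participant timeline), and cluster-level serological rates are calculated before allocation (Allocation), so baseline samples must be read before follow-up samples exist.

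At stake are the reported rate of IgG loss, its comparison between arms, and the inference about secondary infections that the Outcomes section draws from it. The primary seroconversion outcome has its own retest and is not the subject of this point.

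**Working it through.** **Figures in the plan.** There is none for waning: no expected rate, assay sensitivity or specificity, plate-to-plate variation or baseline seroprevalence. The sample size concerns seroconversion only. What is used from it is the head count: 60/0.7 = 85.7, rounded to 86 per cluster; 86 × 68 = 5848 enrolled; 60 × 68 = 4080 after the planned 30% attrition.

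**Assumptions (not from the document).** Baseline prevalence π = 0.40; sensitivity Se = 0.95; specificity Sp = 0.95; errors independent between samples; at first, no new infections.

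**Step 1: who tests positive at baseline.**
- True positives: 0.40 × 0.95 = 0.38
- False positives: 0.60 × 0.05 = 0.03
- Total: 0.41

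**Step 2: apparent waning when nobody wanes.**
- [0.38 × (1 − Se) + 0.03 × Sp] / 0.41 = (0.0190 + 0.0285)/0.41 = 0.0475/0.41 = 11.6%
- Se 0.99, Sp 0.98: (0.396 × 0.01 + 0.012 × 0.98)/0.408 = 3.9%
- Se 0.90, Sp 0.95: (0.36 × 0.10 + 0.03 × 0.95)/0.39 = 16.5%

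**Step 3: effect on a contrast between arms.** With true waning w, the apparent rate is {0.38 × [(1 − w) × 0.05 + w × 0.95] + 0.0285}/0.41.
- w = 0.10: 0.0817/0.41 = 19.9%
- w = 0.15: 0.0988/0.41 = 24.1%
- The difference falls from 5.0 to about 4.2 points, and the ratio from 1.50 to 1.21.

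**Step 4: allowing for new infections.** A falsely positive baseline child who is infected during the interval usually reads positive again. Using the plan's risks as interval risks:
- 0.30: [0.019 + 0.03 × (0.70 × 0.95 + 0.30 × 0.05)]/0.41 = 9.6%
- 0.2115: [0.019 + 0.03 × (0.7885 × 0.95 + 0.2115 × 0.05)]/0.41 = 10.2%

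The artefact is somewhat smaller than in Step 2 but of the same order.

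**Step 5: how much apparent waning is false.** A grid was run over prevalence 20–60%, true waning 2–20% and accuracy from 0.90/0.90 to 0.99/0.99, with seroconversion fixed at 25%. The false share ran from 6% to 96%. At 0.95/0.95 it was 61–81% for 5% true waning and 26–50% for 20%. At 0.99/0.99 it exceeded half only at 2% true waning with prevalence 40% or lower.

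**Step 6: what a retest could do.** At 40% prevalence, 5% true waning, 25% seroconversion and 0.95/0.95, apparent waning is 14.1%, of which 69% is false. If a positive-to-negative result must repeat, with independent errors, apparent waning is 4.4%, of which 10% is false. Independence is the best case for retesting. Even then the repeat keeps only 0.95 × 0.95 = 90% of the true waners first detected.

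**Step 7: workload.** Artefactual pairs per follow-up survey: 0.0475 × 4080 = 194, or 0.0475 × 5848 × 0.7 = 194, so about 195. Allowing for new infections as in Step 4 gives about 161 to 171. With 10% true waning and no new infections, the total to rerun would be 0.0817 × 4080 = 333 pairs.

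**The case against.** The best defence is that this is laboratory detail in a condensed article. Operating procedures are promised for all trial procedures, and nothing says that positive-to-negative pairs will not be rerun. The paired-sample sentence is not limited to seroconverters and is aimed at consistency over time, so it may cover some of these children.

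Part of this stands: the article is silent rather than explicit. But it does state a confirmation rule in detail, and states it for one direction only. The paired-sample sentence does not say which or how many pairs are used, whether they share a plate, or whether a discordant pair changes a classification. Read as written, it checks the laboratory and not the child.

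A second objection is that every input to the size is assumed and that independent errors are the unfavourable case. That is correct. Errors that persist within a child, such as cross-reaction with another arbovirus, repeat at both visits and so create less false waning; a same-plate rerun would not remove them either.

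A reader might also infer that false waners re-enter the next interval as susceptible and contaminate the primary outcome. The article states no such rule. If such a child later appeared to seroconvert, the existing rerun of baseline and follow-up samples would tend to expose the error.

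**Conclusion.** The asymmetry is real. Confirmation is specified for seroconversion and not for the opposite change, although that change is a listed secondary outcome with an inference attached. Waning rates are more exposed to plate-to-plate and single-test error than seroconversion rates.

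The size cannot be fixed from the article. Under 40% prevalence, 95%/95% accuracy and independent errors, about 12% of baseline-positive children would appear to wane with no true waning; at 99%/98% it is about 4%.

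Two stronger readings are tempting and not supported. One is that error produces most of the apparent waning: it can, when true waning is low or the assay only moderately accurate, but not in general. The other is that the artefact hides a difference between arms: in the example it attenuates the contrast and keeps about 4.2 of 5.0 points.

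This is a minor improvement to a secondary outcome.

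**What to change.** Extend the same-plate rerun to both stored samples of every child with an apparent positive-to-negative change, and count waning only when the rerun confirms it. Classify unconfirmed children by the rerun:

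- positive/positive: persistently positive;
- negative/negative: baseline-negative and at risk;
- negative/positive: handled by a rule stated in advance.

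Unconfirmed children should not all be kept as positive. In Step 2, 0.0285/0.0475 = 60% of artefactual waners are baseline false positives and truly IgG-negative.

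Negative/negative children should count as at risk from that survey onward, not for the interval just ended. Baseline false positives who were infected in that interval read positive twice and are never rerun, so adding only the uninfected ones would lower the seroconversion risk artificially.

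If the paired-sample control is already meant to cover these children, it would be enough to say so and to state how discordant results are classified.

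The cost is about 195 artefactual pairs plus the true waners per follow-up survey under the stated assumptions and 30% attrition: several extra ELISA plates and no new blood. Baseline-positive samples must be kept for the rerun. A few true waners will fail to repeat, and errors that persist within a child will remain.

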#### Approach for participant retention

Based on experience in pilot work ranging between 10% [7] to 20% [45] loss to follow-up with 2 visits, we have estimated a 30% rate of attrition in the current study, due to increased length of follow-up (4 follow-up visits). Participation and follow-up will be encouraged by offering at-home visits and the possibility of rescheduling visits when necessary. All data collection milestones will be scheduled in consultation with the local steering committee to determine the best possible time for the community. Advertisement will be made within the community prior the home visits for data collection to inform households of the upcoming visit of the research team. To compensate for losses due to attrition, decreased participation, and potential biological sample losses, we plan a 43% increase in recruitment.

### Data management

The data collected from the entomological and household assessments will be collected electronically on android phones, that have been programmed Open Data Kit (https://opendatakit.org) which is an open source software. This allows integrating questionnaires in a light application with the appropriate skip logic, value restrictions, and data quality checks before a survey can be finalized. Once a survey is complete, the data will be saved locally on the android phone and later with wifi access, will be synchronized via secure sockets layer (SSL) to a secure server with KoBoToolbox (https://www.kobotoolbox.org). Survey data, GPS coordinates of households and of communal *Aedes* breeding sites, and audio recordings from focus groups can be captured by Open Data Kit and then stored on KoboToolbox. This platform has several features including archiving data, descriptive statistics and visualizations of the data, basic maps, with several export formats possible. All other data, such as the laboratory results from the blood and entomological samples, temperature and humidity data, and the qualitative studies will be stored on a secure server with the French Institute for Research on Sustainable Development (IRD).

